## Discussion

We describe a protocol for a three-arm RCT assessing the effectiveness of an intergenerational telephone support intervention compared to the same-generation peer support intervention and to a common control group in reducing SIL for the older adult population after discharge from the ED.

The ED represents an important but unexploited setting to screen for SIL and initiate social interventions. Prior studies have supported the benefit of intergenerational interventions in reducing SIL in older adults in long-term care homes as well as those who were solicited in the community, though these benefits have not been assessed in the post-ED discharge setting, nor have they been compared to the same-generation peer support interventions [7].

The aging process is experienced diversely by different individuals. Thus, a suite of interventions to address SIL may be beneficial. Intergenerational interventions are a potential alternative to peer support interventions for reducing SIL while potentially benefiting student participants as well [7, 26]. In addition, younger intergenerational volunteers could expand the pool to recruit volunteers and broaden the impact of any intervention. Assessing the effectiveness of the intergenerational HOW R U? intervention will inform whether it is beneficial in reducing SIL and whether it can be applied in the ED setting, and increase our understanding of generativity as a modifiable construct for the development of future social interventions.

Limitations of this protocol include the fact that it is restricted to being delivered in the English language and that it requires a telephone at minimum to participate, although greater than 90% of Canadians have access to a telephone including those among the lowest income quartile [27]. In addition, the defined age range of intergenerational volunteers (i.e., 19–39 years of age) is admittedly arbitrary, and intergenerational programs’ age ranges have historically been loosely defined in the literature [9, 28]. As such, the findings of this study are not generalizable to intergenerational programming involving volunteers of adjacent generations (i.e., age 39–59). Potential confounders of the primary outcome measures include the individual interpersonal relationships between participant and volunteer, as well as potential differences in preference and ultimate assignment to intergenerational or same-generation peer support intervention. A follow-up RCT could compare the impact of preference accommodation versus a random selection of social intervention on reducing SIL. In addition, while social desirability bias is known to complicate research on stigmatized conditions such as isolation and loneliness, the De Jong scale is an indirect measure of loneliness to minimize this bias. Furthermore, outcomes among the intervention and control subjects will be evaluated using the same scale following randomization, thus mitigating the impact of this bias.

Given the lack of studies on modifying generativity, one area of uncertainty is in the ability of the present intergenerational intervention design to increase self-perceptions of generativity. Few studies have looked at self-perceptions of generativity as a modifiable construct, and there is no standard method of promoting these self-perceptions used in the literature. However, the secondary outcome measure of “perceived benefit to the volunteer” may serve as an adjunct for measuring generativity [7]. Lastly, though not formally assessed in this RCT, further studies may measure the potential benefits of modifying attitudes towards aging in young volunteers participating in intergenerational interventions.

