Key inclusion and exclusion criteria	Inclusion Criteria 1. Community-dwelling person 70 years of age and older receiving care from the ED, Family Medicine or Geriatric clinics at the two participating sites (MSH, NYGH) 2. Baseline de Jong loneliness score of 2.0 will be required for participating in the trial Exclusion Criteria 1. Age less than 70 years of age 2. Patients with communication problems (critically ill, unconscious, language barrier, speech impairment or otherwise unable to provide consent) or admission to a hospital for greater than 72 h) 3. Patients with severe cognitive impairment or those with living in nursing homes who are dependent on others for their activities of daily living 4. Patients without any mobile phone or landline Volunteer Inclusion Criteria 1. Peer-support volunteers will be 60 years of age or older 2. Intergenerational volunteers will be between 19–39 years of age
Study type	Interventional Allocation: Randomized interventional model. Parallel assignment. Outcome assessor masking Primary purpose: Supportive Care
Date of first enrolment	November 1, 2021
Target sample size	141
Recruitment status	Recruiting
Primary outcome(s)	1. Change in loneliness using De Jong Gierveld 6-item Loneliness Scale from baseline to 12 weeks
Key secondary outcomes	1. Change in loneliness using De Jong Gierveld 6-item Loneliness Scale from baseline to 24 weeks 2. Change in perceived social support using Lubben Social Network Scale from baseline to 12 and 24 weeks 3. Change in mood using Geriatric Depression Scale from baseline to 12 and 24 weeks 4. Change in baseline cognition using “Brief Alzheimer’s Screening Test” from baseline to 12 and 24 weeks 5. Change in Quality of Life using Euro-Qual 5 Dimensions 5 Levels from baseline to 12 and 24 weeks 6. Change in Functional Status using Older Americans Resource Scale from baseline to 12 and 24 weeks 7. Change in self-perceptions of generativity using Loyola Generativity Scale from baseline to 12 and 24 weeks 8. Perceived benefit to participant at 12 and 24 weeks 9. Perceived benefit to volunteer at 12 and 24 weeks

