#### Same-generation peer support intervention

The same-generation peer support intervention group will receive the current HOW R U? intervention delivered by similarly aged peer volunteers. The HOW R U? intervention consists of weekly 30-min telephone-support calls over 12 weeks. The focus of each interaction is a strength-based approach including encouraging the participant to identify goals to improve SIL such as integrating with community activities [4]. Volunteers will reassess these goals each week and will maintain progress logs for each participant consisting of session dates, session duration, sessions missed, and any participant drop-outs.

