#### Intergenerational intervention

The intergenerational intervention group will receive the HOW R U? intervention over the telephone as described above and delivered by trained intergenerational volunteers. Unique to the intergenerational intervention, informal service-learning goals will be assigned to the student volunteers and simultaneously made known to their participants. These include reflecting on the older adult’s experience of navigating the healthcare system, identifying negative ageist perceptions and stereotypes associated with older adults and the aging process, and risk factors for SIL among older adults. The purpose of these additional objectives is to facilitate a sense of mutual benefit and self-perceptions of generativity in the older adult participants consistent with Erikson’s theory [16].

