### Sample size and power

Each group will consist of a sample of 47 subjects which will detect a 13.9–28.1% difference between the treatment and control groups in the proportion of people who improve by one category (e.g., from severe loneliness to moderate-to-severe loneliness) with a power greater than 80%. This assumes that up to 15% of control group participants may have a spontaneous improvement in loneliness categories. With these sample sizes, three comparisons may be made: intergenerational intervention to the control group, same-generation peer support intervention to the control group, and intergenerational to the same-generation peer support intervention.

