### Analysis

All analyses will use SAS Version 9.4 (SAS Institute, Cary, NC, USA). A two-sample two-sided test of proportions will be used to assess the primary outcome of loneliness in the control group versus the intergenerational HOW R U?, and the control group versus the same-generation peer support HOW R U? intervention. Improvements in the binary outcome of the loneliness category of the De Jong Loneliness Scale will be assessed using a logistic regression model, and results will be reported as odds ratios with the corresponding 95% confidence intervals. The variance inflation factor (VIF) will be calculated to assess for multicollinearity before the logistic regression model is built such that if two variables are highly correlated (i.e., VIF > 4 or tolerance < 0.25), only one of the two variables is retained for the final model. To compare the secondary outcomes, they will be reported as means with corresponding 95% confidence intervals.

Potential missing data will be managed as follows. For logistic regression, participants with more than 15% missing data for confounding variables will be excluded from the analysis. Note that in the main trial, less than 5% of participants would have been excluded. For participants with less than 15% missing data, we will use imputation for confounding variables. Participants with missing outcome data will be excluded from analysis (i.e., lost to follow-up). Note that after two-thirds of the participants have been enrolled, we will assess the loss-to-follow-up rate and adjust the enrollment accordingly. For example, if the lost-to-follow-up rate is 20%, we will increase the enrolment by 20%. To manage protocol nonadherence, participants will be analyzed using intention-to-treat analysis regardless of their adherence to the protocol.

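### The primary analysis and sample size assume independent participants; if volunteers in the active arms serve more than one participant, standard errors will be too small

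*Protocol article*

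**What the plan says.** **Delivery.** Under Intervention, research assistants match volunteers to participants after randomisation, on gender preference and shared interests. Each active arm then receives 12 weekly calls. Under Same-generation peer support intervention, volunteers "will maintain progress logs for each participant". Under Intergenerational intervention, the students' learning goals are "simultaneously made known to their participants". Under Waitlist control, that arm receives no intervention for 24 weeks. No section gives the number of participants per volunteer or sets one-to-one pairing.

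**Analysis.** "A two-sample two-sided test of proportions will be used to assess the primary outcome of loneliness", for control versus each active arm. Improvement in loneliness category is also modelled by logistic regression. No volunteer term, clustered variance or intraclass correlation is mentioned.

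**Sample size.** "Each group will consist of a sample of 47 subjects which will detect a 13.9–28.1% difference between the treatment and control groups". "This assumes that up to 15% of control group participants may have a spontaneous improvement in loneliness categories". Table 2 gives "Target sample size 141", which is 3 × 47 with no inflation.

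**Limitations.** In the Discussion: "Potential confounders of the primary outcome measures include the individual interpersonal relationships between participant and volunteer".

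**The concern.** In the active arms the treatment is a 12-week relationship with a particular volunteer. If one volunteer serves several participants, their outcomes may share that volunteer's skill, warmth or reliability and so be positively correlated. The waitlist arm has no such structure, so the trial would be partially nested. A test of proportions and an ordinary logistic regression count every participant as independent information. Under sharing they would give intervals that are too narrow and p-values that are too small.

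Intergenerational versus peer support, the second primary aim under Study purpose, would be most exposed. Both its arms would be clustered, and volunteer generation varies only between volunteers. A few unusually good or poor volunteers could then be mistaken for an effect of generation.

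The Discussion also calls the relationship a confounder. It arises after randomisation and is part of how treatment is delivered, so it cannot confound a randomised contrast. Because the Analysis section refers to adjustment for confounding variables, the label points towards covariate adjustment, when the statistical issue is a possible variance component.

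**Working it through.** **1. The plan's own figure.** Inputs from Sample size and power: control improvement 15%, difference 28.1 points (so 43.1%), power 80%. Two-sided alpha is not stated; 0.05 is assumed from the 95% intervals.

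- Mean proportion = (0.15 + 0.431)/2 = 0.2905.
- Uncorrected n = [1.96·√(2 × 0.2905 × 0.7095) + 0.8416·√(0.15 × 0.85 + 0.431 × 0.569)]² / 0.281² = (1.258 + 0.514)² / 0.0790 = 39.8, so 40.
- With continuity correction, n = (39.8/4)·[1 + √(1 + 4/(39.8 × 0.281))]² = 46.6, so **47**.

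The stated 47 is therefore reproduced at the 28.1% end by a formula that assumes independence. The 13.9% end depends on the test convention used and has no bearing on this point.

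**2. Design effect.** The documents give neither participants per volunteer (m) nor the intraclass correlation (ICC). Assumed ranges: m = 2 to 5, ICC = 0.02 to 0.10. With equal caseloads, DE = 1 + (m − 1)·ICC.

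- m = 2, ICC 0.02: DE = 1.02; effective n = 47/1.02 = 46.
- m = 5, ICC 0.10: DE = 1.40; effective n = 47/1.40 = 34.
- m = 1: DE = 1.00; nothing changes.

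**3. Ratio of true to naive standard error.** With equal variances, the ratio is √((1 + DE)/2) for active versus waitlist (one arm clustered) and √DE for intergenerational versus peer (both clustered).

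**4. True type I error of a nominal 5% test** = 2·[1 − Φ(1.96/ratio)].

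| m | ICC | DE | Ratio vs waitlist | Type I error vs waitlist | Ratio IG vs peer | Type I error IG vs peer |
|---|---|---|---|---|---|---|
| 1 | any | 1.00 | 1.000 | 5.0% | 1.000 | 5.0% |
| 2 | 0.02 | 1.02 | 1.005 | 5.1% | 1.010 | 5.2% |
| 2 | 0.05 | 1.05 | 1.012 | 5.3% | 1.025 | 5.6% |
| 5 | 0.05 | 1.20 | 1.049 | 6.2% | 1.095 | 7.4% |
| 5 | 0.10 | 1.40 | 1.095 | 7.4% | 1.183 | 9.8% |

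At m = 3 and ICC 0.05, DE = 1.10 and the head-to-head ratio is √1.10 = 1.049. For m of 2 to 3 with ICC up to 0.05, the understatement is therefore under 5%.

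**5. Power against waitlist, 15% versus 43.1%, n = 47,** using the uncorrected formula with the active-arm variance multiplied by DE: 86.3% under independence, 85.3% at m = 2 and ICC 0.05, 82.5% at m = 5 and ICC 0.05, 78.8% at m = 5 and ICC 0.10.

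**6. Is sharing plausible?** Strict one-to-one pairing needs 2 × 47 = 94 trained volunteers. Recruitment runs from November 2021 to about February 2024, some 27 months, while each course of calls lasts 12 weeks. A volunteer could therefore serve several participants in succession. This makes reuse plausible but does not show that it happens.

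**The case against.** A reader might infer that volunteers are shared and that the standard errors will be too small. The documents do not support either as fact. Both need m above 1 and a positive ICC, and neither figure is given. The log wording fits one log per pair equally well, and the plural in the learning-goals sentence says nothing about caseload.

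The limitation quoted is about individual relationships. Variation peculiar to a pair is residual variance and creates no correlation between two participants of the same volunteer; only a shared volunteer effect does. That sentence therefore shows that the authors expect the relationship to matter, not that outcomes are clustered.

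The head-to-head contrast, where the effect would be largest, is given no test of proportions under Analysis. The upper figure of 9.8% thus describes what would happen if the same naive method were extended to it. For the two tests actually named, the range is 5.1–7.4%.

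Caseload and a provider term may also be set out in a fuller document that is not shown. That is fair, and silence on them alone would not be a finding.

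All of this stands, and it makes the point conditional. It does not remove it: the article fixes a primary test that cannot carry a volunteer effect, and nothing in it rules out sharing.

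**Conclusion.** The concern holds as a conditional one. The stated primary analysis and the 47 per arm rest on independence, in a design where two arms are delivered by volunteers and one is not, and where one-to-one pairing is not set. If volunteers serve more than one participant and the ICC is positive, inference is too optimistic, more so for intergenerational versus peer than for either comparison with waitlist.

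The size rests wholly on the assumed m and ICC. It ranges from nothing at m = 1, through a minor effect at m of 2 to 3 with ICC up to 0.05, to a type I error of 7.4% (versus waitlist) or 9.8% (head-to-head) at m = 5 and ICC 0.10. The calculations use equal caseloads and a normal approximation. This is not a demonstrated error in the results to come, but it is a weakness in the stated method that is cheap to remove. Separately, and whatever the caseload, confounder is the wrong term for a relationship formed after randomisation.

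**What to change.** - **Record** the volunteer's identifier for every active-arm participant. The logs are described as holding call dates, times, durations, missed sessions and drop-outs; the article does not say that they hold an identifier.
- **Analysis section:** base primary inference on the logistic model with small-sample-corrected cluster-robust standard errors by volunteer, each waitlist participant being a cluster of one. The alternative is a partially nested model with a volunteer random effect in the active arms only. Choose one in advance, and apply it also to intergenerational versus peer.
- **Report** the number of volunteers and the participants per volunteer in each active arm. If every volunteer served one participant, one sentence closes the matter.
- **Discussion:** describe the participant–volunteer relationship as a post-randomisation provider effect, not a confounder to be adjusted for.

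**Cost.** A few lines of plan text and SAS code, with no change to recruitment or treatment. Intervals will be slightly wider if volunteers are shared. If most volunteers serve only one or two participants, a volunteer variance may be poorly estimated or come out as zero, which favours the cluster-robust option.

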## Conclusions

This protocol is part of a program of research following the ORBIT model for complex behavioral interventions. As such, the findings of this three-arm RCT have been informed by our previous research and will inform future research exploring which intervention characteristics are most effective in reducing SIL for specific older adult subgroups. Future RCTs will assess whether the element of patient choice between different demographics of groups yields differences in reducing loneliness.

## Trial status

Protocol version: 2023-Oct-03 Version 2.

Date of Recruitment Start: November 1, 2021.

Approximate Date of Recruitment Completion: February 1, 2024.

## Data Availability

Not applicable.

## Appendix 1

### Theoretical framework of intergenerational intervention

The modified intergenerational HOW R U? intervention is grounded in Erikson’s theory of psychosocial development which posits that individuals progress through psychological stages each with a developmental crisis that is either successfully resolved or contributes to negative personality development. During middle adulthood, generativity, defined by Erikson as “the interest in establishing and guiding the next generation,” or in other words “the need to be needed” is the primary goal to be met at this stage [29]. This generativity manifests as mentoring, caretaking, parenting, and ultimately contributing meaningfully to the lives of others. Failure to do so leads to “stagnation.” Eriksonian theory also suggests that providing a renewed sense of purpose may result in “engaging in self-management to remain autonomous rather than passively allowing others to manage their care” [16].

Erikson further believed that the need for generativity extends well into late life as “grand generativity,” defined as a continuation of the need to assist the next generation into older adulthood to provide role modeling to young people while simultaneously benefiting from interactions with the young [30, 31]. This type of reciprocal relationship is encapsulated in intergenerational programs, defined as involving social interactions among members of the younger and older generations and intergenerational exchange [32]. Whereas volunteering places emphasis on the unidirectional benefit to the recipient, intergenerational service learning promotes equal emphasis of benefit to the volunteer and participant and, in doing so, enhances participants’ self-perceptions of generativity. In turn, greater perceptions of generativity are associated with improved mental and physical well-being and lower levels of negative affect and depressed mood [7]. Thus, in keeping with Eriksonian theory, adding service-learning goals and making them known to both student volunteer and participant promote self-perceptions of generativity among participants that are hypothesized to reduce feelings of SIL.

## Appendix 3

### Description of assessment tools used for outcome measures

#### Primary outcome measure scales

1. De Jong 6-item Loneliness Scale: The De Jong scale has been extensively validated in older populations and is divided into four clinically relevant categories: 6—severe loneliness, 4–5—moderate-to-severe loneliness, 2–3—low loneliness, and 0–1—no loneliness [12].

#### Secondary outcome measure scales

1. Lubben’s 6-item Social Network Scale: The Lubben’s Social Network Scale is a measure of perceived social support received from family and friends and consists of six items each of which is scored from 0 to 5: none = 0, one = 1, two = 2, three or four = 3, five through eight = 4, nine or more = 5. The total score ranges from 0 to 30, and a score of 12 or lower indicates a status of “at-risk” for social isolation [33]. The Lubben’s Social Networks Scale has been shown to be a reliable and valid instrument among older adults [33].
2. 5-item Geriatric Depression Scale: The 5-item Geriatric Depression Scale is a scale of mood that is extensively validated in older populations to screen for depression [19]. Scores range from 0 to 5. A score of 0–1 is considered normal suggesting that the patient is not depressed, and a score of 2 or higher is considered indicative of possible depression with higher scores indicating higher severity of depression [19].
3. Brief Alzheimer’s Screening Test: The Brief Alzheimer’s Screening test is a test that has been validated retrospectively on a cohort of older adults and used to assess cognitive performance and to screen for dementia [34]. There are four questions which are scored correct or incorrect and inputted numerically into an algebraic equation to distinguish normal older adults with those with dementia. A score of 26 or less is consistent with dementia [34].
4. Euro-Qual 5 Dimensions 5 Levels (EQ-5D-5L): The EQ-5D-5L is used to assess perceived health-related quality of life in the areas of self-care, mobility, usual activities, pain/discomfort, and anxiety/depression [21]. In each dimension, quality of life can be measured from 1 (best quality of life) to 5 (worst quality of life), giving a possible score of 5–25. A higher score indicates a worse quality of life. This instrument has been used and shown to be feasible in the elderly population [35].
5. Older Americans Resource Scale (OARS): The Older Americans Resource Scale is used to assess functional status and has been shown validity and reliability in the elderly population [36]. It consists of 7 activities of daily living (ADL) questions and 7 instrumental activities of daily living (IADL) all rated as “without any help” (2 points), “with some help” (1 point), or “completely unable” (0 points). The ADL and IADL scores can be used separately or combined to produce an overall OARS score from 0 to 28.
6. Loyola Generativity Scale (LGS): The Loyola Generativity Scale measuring generativity is a 20-item scale with each question answered 0 = statement never applies to you, 1 = statement only occasionally or seldom applies to you, 2 = statement applies to you fairly often, or 3 = statement applies to you very often or nearly always. The higher the score, the greater the sense of generativity. The LGS has demonstrated good interrater reliability as well as responsiveness in trials of older adults [24, 25].

